### Study Population

The following 2 groups of participants will be included in the study: persons affected by leprosy (for the participatory development of the interventions) and community members (the target group of the interventions).

### Inclusion and Exclusion Criteria

Individuals aged 18 years or older will be included in this study. Individuals who do not speak Nigerian Pidgin or Hausa and who are unable or unwilling to give informed consent will be excluded from the study.

### Study Duration and Sample Size Calculation

This study’s duration will be 2 years. The sample size for the various components of the study is as follows. (1) A total of 200 community members (100 for each language per study area) will be included in the cross-cultural validation of the Explanatory Model Interview Catalogue Community Stigma Scale (EMIC-CSS) and Social Distance Scale (SDS), while 100 persons affected by leprosy (50 for each language per study area) will be included in the cross-cultural validation of the Internalized Stigma of Mental Illness (ISMI) scale and Rosenberg Self-Esteem Scale (RSES; see below). (2) A total of 770 community members will be included in the baseline and follow-up questionnaire interviews. This means a random sample of at least 385 persons in Taraba State (northern Nigeria) and at least 385 persons in Cross River State (southern Nigeria), which will consist of 114 in the audio intervention group, 114 in the written material intervention group, and 157 in the control group in each region.

This RCT will have three arms: (1) an audio-delivered intervention group, (2) a written material intervention group, and (3) a control group. The sample size calculation is based on 2 calculations. The intervention group calculation is based on an estimate of the difference in knowledge improvement between the audio-delivered intervention and the written material intervention groups. We used data from a perception study in India. In this study, postintervention scores improved by 12.5% after a poster intervention and community meetings. We estimate that the effect of posters alone would be an increase of 10%. We want to be able to detect an improvement of at least 15% between the audio-delivered and the written material intervention groups. The sample size of the intervention group is therefore based on a proportion 1 of 10 (estimated percentage of improvement in knowledge of leprosy in the written intervention group) and a proportion 2 of 25 (ie, an improvement of 15% or more). With a power of 80%, a significance level of .05, and a 15% loss to follow-up, 114 participants are needed in each intervention group.

We expect an increase of 2% in the knowledge score in the control group. The control group calculation is therefore as follows: proportion 1:10, proportion 2:2, power 80%, significance .05, and 15% loss to follow-up, resulting in 157 participants.

A total of 25 people will be included in the participatory development of the material [41]. In each state, these will consist of 10 persons affected by leprosy and 2-3 community members. Semistructured interviews will be conducted until data saturation is reached.

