## Methods

### Study Design

We will conduct a cross-sectional study (intervention development) and a 3-arm cluster randomized controlled trial (RCT; intervention implementation and evaluation). The three arms consist of (1) an intervention group who will receive the audio-delivered intervention, (2) an intervention group who will receive the written intervention (poster or flyer), and (3) a control group who will not receive any intervention.

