### Participant Recruitment and Follow-Up

Persons affected by leprosy and community members will be selected based on purposive sampling. They will develop the content of the interventions. This is therefore, ideally, a diverse group of people who represent multiple perspectives. We will select participants based on purposive sampling to ensure adequate representation of age, gender, and villages.

The intervention will be implemented in North and South Nigeria, 2 areas that are very different. Therefore, we will cluster-randomize the interventions to ensure comparable groups are included in both areas. There are three different “groups” in each site (North and South): (1) the audio-delivered intervention, (2) the written materials intervention, and (3) no intervention (control group).

We will select 3 LGAs in North and South Nigeria (6 in total); each LGA will have either the audio-delivered or the written intervention or be a control group. The three LGAs per area will be selected based on their similarity in terms of literacy rate and endemicity of leprosy.

The interventions will be randomly allocated to clusters (LGAs) based on a random numbers list. This is a 2-stage random sampling. We will select a random sample of LGAs and a random sample of participants within each LGA. The participants in each LGA will be selected using the “spin the bottle” approach: a bottle will be spun in front of the most central place in the village (rural area) or neighborhood (urban area); the direction the bottle points at is the direction we start walking and counting. The first house to be included is selected by casting a die. Participant selection will be done by proportional sampling among the clusters. We will include the same participants at baseline and follow-up (a paired sample). This study protocol is reported in accordance with the SPIRIT statement (see checklist in Multimedia Appendix 1). The timeline schedule for participants during the study period is represented in Table 1, and a schematic description of the study flow chart is depicted in Figure 1.

**Table 1 table1:** Study schedule for enrollment, intervention, and assessment.

Schedule				Study period and time point										
				Enrollment		Allocation		Postallocation						Close out
				t_–1_		t_0_ (month 0)		t_1_ (baseline)		t_2_ (intervention)		t_3_ (6 months follow-up)		t_4_

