### Limitations

There are inherent limitations associated with cluster-randomized studies, such as cluster size variability. With the challenge of achieving uniform cluster sizes, variability in cluster size could impact the generalizability of the results. Additionally, there is a risk of contamination between clusters; however, this is minimal given the geographic distance between the study cluster locations.

The study sites were purposefully selected due to their similarity in having a high prevalence of leprosy and G2Ds; thus, the findings from this study may not be generalizable to the entire Nigerian populace.

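### The sample size treats participants as independent although only six LGAs are randomised, two per arm, so the stated 80% power is not delivered

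*Protocol article*

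**What the plan says.** Study Design describes "a 3-arm cluster randomized controlled trial (RCT; intervention implementation and evaluation". Participant Recruitment and Follow-Up makes the LGA the unit of allocation: "The interventions will be randomly allocated to clusters (LGAs) based on a random numbers list". The number of clusters is fixed there too: "We will select 3 LGAs in North and South Nigeria (6 in total); each LGA will have either the audio-delivered or the written intervention", or else serves as control. That is one LGA per arm in each state and two per arm overall.

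Study Duration and Sample Size Calculation derives the numbers from two comparisons of proportions. For audio versus written, the written group is set at 10% and the audio group at "a proportion 2 of 25 (ie, an improvement of 15% or more"). The result is: "With a power of 80%, a significance level of .05, and a 15% loss to follow-up, 114 participants are needed in each intervention group". For the control group the inputs and result are "proportion 1:10, proportion 2:2, power 80%, significance .05, and 15% loss to follow-up, resulting in 157 participants". These are then applied by state, as "114 in the audio intervention group, 114 in the written material intervention group, and 157 in the control group in each region", for a total of 770. The inputs listed are two proportions, power, significance level and loss to follow-up, and nothing else.

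Limitations names two cluster issues. One is unequal cluster size, where "variability in cluster size could impact the generalizability of the results". The other is contamination between clusters, judged minimal. Loss of precision is not mentioned.

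**The concern.** People in the same LGA tend to answer alike, and everyone in an LGA receives the same intervention. The information about an arm difference is therefore limited by the number of LGAs as well as the number of people. A calculation that treats people as independent overstates precision through two separate routes:

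- the variance is inflated by the design effect;
- with two LGAs per arm, the between-LGA variance is estimated on very few degrees of freedom, which pushes the critical value far above 1.96.

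The intervention groups are sized on audio versus written. Readers will use the printed 80% to judge what a non-significant result on that comparison means. If true power is well below 80%, such a result says little either way.

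**Working it through.** **Step 1. Reproduce the printed sizes** (two-sided 0.05, 80% power, no clustering term).

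Pooled-variance form: n = [1.96·√(2p̄(1−p̄)) + 0.842·√(p₁(1−p₁)+p₂(1−p₂))]² / (p₁−p₂)².

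- 10% vs 25%: n = 99.54; × 1.15 = 114.5 (printed: 114)
- 10% vs 2%: n = 137.15; × 1.15 = 157.7 (printed: 157)

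Both match after truncation. The unpooled form, n = 7.849·[p₁(1−p₁)+p₂(1−p₂)]/(p₁−p₂)², divided by 0.85, gives 96.8/0.85 = 113.9 and 134.4/0.85 = 158.1, which is also close. By either route the design effect is 1, and no room is left for a hidden clustering allowance.

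**Step 2. Inputs for the recalculation.**

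- Retained per LGA: m = 114 × 0.85 ≈ 97, so 194 per intervention arm over both states.
- Proportions 0.10 and 0.25; summed variance 0.09 + 0.1875 = 0.2775.
- ICC: not given in the article. Assumed 0.01, 0.02 and 0.05, with 0 as the best case.
- DEFF = 1 + (m−1)·ICC = 1 + 96·ICC.

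**Step 3. Within one state, as the plan sizes it.** Effective n per arm = 97/DEFF, put into the two-proportion power formula. This is generous: with one LGA per arm in a state, arm and LGA are fully confounded, and the calculation assumes that the LGA variance is known.

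**Step 4. Both states pooled, LGA-level test.** SE = √(0.2775/194 × DEFF). The residual df are 6 LGA means − 3 arms − 1 state term = 2, with critical value 4.303. Power comes from the noncentral t with noncentrality 0.15/SE. The 95% CI half-width is 4.303·SE.

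| ICC | DEFF | Effective n per arm, one state | Power, one state | Pooled SE | 0.15/SE | Power, pooled, 2 df | CI half-width (points) |
|---|---|---|---|---|---|---|---|
| 0 | 1.00 | 97 | 79% | 0.0378 | 3.97 | 56% | 16 |
| 0.01 | 1.96 | 49.5 | 50% | 0.0529 | 2.83 | 36% | 23 |
| 0.02 | 2.92 | 33.2 | 36% | 0.0646 | 2.32 | 27% | 28 |
| 0.05 | 5.80 | 16.7 | 20% | 0.0911 | 1.65 | 17% | 39 |

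**Step 5. Detectable difference.** Power of 80% on 2 df needs a noncentrality of about 5.65. Holding the variance at 0.2775, the difference detectable with 80% power is 5.65·SE: about 21 points at ICC 0, and 30, 37 and 51 points at ICC 0.01, 0.02 and 0.05. The planned difference is 15.

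**Step 6. Written versus control.** With 97 and 133 (157 × 0.85) retained per LGA, SE = √[0.09/194·(1+96·ICC) + 0.0196/266·(1+132·ICC)]. At ICC 0, 0.01 and 0.02 this is 0.0232, 0.0329 and 0.0403. For an 8-point difference, power on 2 df is 47%, 29% and 22%.

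**Step 7. Would more people per LGA help?** Effective n per arm is 2m/(1+(m−1)·ICC), which cannot exceed 2/ICC however large m becomes: 100 at ICC 0.02 and 40 at 0.05. The limit is the number of LGAs.

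**The case against.** The strongest defence is the doubling. The calculated 114 is enrolled in each state, so each intervention arm has 228, and the article does not say that the primary test is run by state. If both states are pooled and only a design effect is applied, with a normal reference, power is about 97.5% at ICC 0, 80% at 0.01, 63% at 0.02 and 36% at 0.05. On that view the 80% survives up to an ICC of about 0.01. This is true as arithmetic, but the doubling is not presented as a clustering allowance. The normal reference also takes the between-LGA variance as known, when two LGAs per arm can barely estimate it.

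The 2 df are a model choice. Without a state term there are 3 df, and power is 75% at ICC 0 and 49%, 36% and 21% at 0.01, 0.02 and 0.05. That is better, but still below 80% throughout. If a one-sided 0.05 test were intended (the analysis section names a one-tailed t test), power at ICC 0.01 would be 58% on 2 df or 70% on 3 df. The printed sizes, however, reproduce only as two-sided.

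Three further points stand as qualifications:

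- The same people are measured at baseline and follow-up, which might reduce the between-LGA variance. The article gives no figure for this.
- An ICC estimated from six LGAs will be imprecise, and baseline data give the ICC of a level rather than of an improvement.
- The tests listed in Data Management and Data Analysis work on individuals. If used as they stand, they would show more apparent power but inflate the type I error, to about 16% at ICC 0.01 and 25% at 0.02. That is a companion problem and does not support the 80%.

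**Conclusion.** The concern holds. The printed sizes are those of an individually randomised trial, while the design randomises six LGAs, so the 80% power statement is wrong for this trial. An LGA-level two-sided test on 2 or 3 df misses 80% for a 15-point difference even if the ICC is zero (56% or 75%). At ICC 0.01 to 0.05 it gives 36% to 17% on 2 df, or 49% to 21% on 3 df. The size of the shortfall rests on the assumed ICC, on 97 retained per LGA and on the planned 10% and 25%. The existence of the shortfall does not depend on the ICC. A non-significant audio-versus-written result would be uninformative. The power statement must be corrected before the results are interpreted.

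**What to change.** Keep the enrolled sample and rewrite the power paragraph:

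1. State the number of clusters (two LGAs per arm, one per arm in each state) and use DEFF = 1 + (m−1)·ICC.
2. Estimate the ICC and SD from the baseline data already collected (811 respondents). Because six LGAs give an imprecise estimate, report results over a range as well, for example 0.01 to 0.05.
3. Use a t reference on 2 df, say which LGA-level analysis this refers to, and make the analysis section agree with it.
4. Replace the 80% claim with the resulting power and detectable difference, and say that a non-significant result will not be read as equivalence.

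Possible wording, to be updated with the baseline ICC:

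> The sizes of 114 and 157 were derived for independent individuals. Allowing for randomisation of two LGAs per arm, with 97 participants retained per LGA in the intervention arms and a two-sided 5% test on 2 df, power to detect 25% versus 10% is about 36%, 27% and 17% at assumed ICCs of 0.01, 0.02 and 0.05. A non-significant difference will not be interpreted as equivalence of the two interventions.

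The cost is one paragraph and one calculation on data in hand. At submission neither implementation of the intervention nor data analysis had begun. No participants are added. The price is a much less favourable power figure. Restoring 80% would take more LGAs per arm; adding people within the same six cannot do it.

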### Data Management and Data Analysis

Quantitative data collection will be done using electronic forms developed in the Open Data Kit, and all data will be securely stored in the cloud with access only to the research team. The recordings of the in-depth interviews and FGDs will be transcribed to the local languages, translated to English, and analyzed by 2 independent researchers using open, inductive coding and content analysis. Similar phrases with recurring themes will be coded in NVivo (QSR International). Quantitative data will be collected in the KoboCollect (Kobo Inc) mobile phone app. Data analysis will be done in the software package SPSS Statistics (SPSS Inc). Simple descriptive methods will be used to generate a demographic profile of the study sample. Differences between participants in the groups (audio, written materials, and control groups) will be evaluated using the Mann-Whitney *U* test or 1-tailed *t* test for continuous variables and the chi-square statistic for categorical variables. The mean (SD) or median (IQR), depending on the distribution of the data, of the total scores of the scales used will be calculated per intervention area. Stepwise multivariate regression with backward elimination will be done to examine what factors will have an independent effect on the outcomes. We will calculate the percentage change and corresponding 95% CI before and after the interventions are implemented and the statistical significance of this difference using a z test for differences between proportions. Effect sizes will also be calculated. If necessary, we will correct for differences in demographic information between study arms using quantile regression. We will compare the differences in follow-up assessment between the audio-delivered and written interventions. The knowledge gaps, beliefs, misconceptions, fears, etc identified in the baseline study will be summarized into a narrative review and will be used by the persons affected by leprosy group as input for the development of the content of the interventions. The most appropriate modes of delivery will be determined based on the communication needs assessment that will be conducted as part of the baseline study. The interventions will be developed using participatory methods.

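### The 10% versus 2% calculation needs 157 in both written and control; with only 114 in written, per-region power is about 68–78%, not 80%, before clustering

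*Protocol article*

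**What the plan says.** All of the figures are in the protocol article under Study Duration and Sample Size Calculation. Two calculations are given.

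- **Audio versus written**, 25% against 10%: "With a power of 80%, a significance level of .05, and a 15% loss to follow-up, 114 participants are needed in each intervention group".
- **The control group calculation**, 10% against 2%: "proportion 1:10, proportion 2:2, power 80%, significance .05, and 15% loss to follow-up, resulting in 157 participants". The 2% is the control assumption: "We expect an increase of 2% in the knowledge score in the control group". The 10% matches the estimate for the written arm: "We estimate that the effect of posters alone would be an increase of 10" (per cent).

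The resulting sizes are "114 in the audio intervention group, 114 in the written material intervention group, and 157 in the control group in each region". That is 114 + 114 + 157 = 385 per state and 2 × 385 = 770 overall, in line with "A total of 770 community members will be included in the baseline and follow-up questionnaire interviews".

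The section does not give the formula, the sidedness, the method of inflating for loss, or whether the 80% is meant for each region or for the whole trial. Under Participant Recruitment and Follow-Up, each region has three local government areas (LGAs), one per arm, so six are randomised in all. The sample size calculation contains no allowance for clustering.

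**The concern.** A two-proportion calculation with equal arms returns one number that both arms must reach. Here the number from the 10% versus 2% comparison goes to control alone, while written keeps a smaller number derived for a different comparison. No calculation in the document supports 114 against 157.

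The shortfall also falls on the less favourable arm. The binomial variance is 0.10 × 0.90 = 0.09 in written and 0.02 × 0.98 = 0.0196 in control, so precision depends mostly on the written arm.

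Written versus control is one of the comparisons behind the primary objective, which covers both audio and written education. A null result for it within one region could be read as coming from a comparison with 80% power when the planned sizes do not provide that.

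**Working it through.** **Inputs from the sample size section.** Written 10%, control 2%, audio 25%; α = 0.05; power 80%; loss 15%; 114, 114 and 157 per region. Two-sided testing is inferred. The analysis section mentions a "Mann-Whitney *U* test or 1-tailed *t* test" for continuous variables, but none of the one-sided variants tried reproduces both 114 and 157.

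**Step 1: reproduce the plan's figures (equal arms, two-sided).**

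Unpooled: n = (1.96 + 0.842)² × [p₁(1−p₁) + p₂(1−p₂)] / (p₁−p₂)².

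- 10% vs 25%: n = 96.8 per group; 96.8/0.85 = 113.9, which is 114.
- 10% vs 2%: n = 134.4 per group; 134.4/0.85 = 158.1 (or 134/0.85 = 157.6, truncated to 157).

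Pooled variance under the null gives n = 99.54 and 137.15 per group. Multiplied by 1.15 these become 114.5 and 157.7, which truncate to 114 and 157.

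Both routes come within about one participant of the plan's figures. In both, 157 is a per-group number.

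**Step 2: numbers analysed per region.** Written 114 × 0.85 = 96.9, about 97. Control 157 × 0.85 = 133.45, about 133.

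**Step 3: power at 10% vs 2% with 97 and 133.**

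- SE under the alternative: √(0.09/97 + 0.0196/133) = 0.0328.
- Unpooled: Φ(0.08/0.0328 − 1.96) = Φ(0.48) = 68.4%.
- Pooled: p̄ = (97 × 0.10 + 133 × 0.02)/230 = 0.0537; SE₀ = √[0.0537 × 0.9463 × (1/97 + 1/133)] = 0.0301; Φ((0.08 − 1.96 × 0.0301)/0.0328) = 73.9%.
- Exact enumeration of the uncorrected Pearson test: 77.8%.

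**Step 4: comparisons.**

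| Analysed, written vs control | Unpooled | Pooled |
|---|---|---|
| 97 vs 133 (one region, as planned) | 68.4% | 73.9% |
| 133 vs 133 (157 enrolled in both) | 79.6% | 78.8% |
| 114 vs 157 (one region, no loss) | 75.4% | 80.2% |
| 194 vs 267 (both regions, independence) | 93.2% | 95.1% |

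With 97 analysed in written, the pooled formula needs about 179 analysed controls for 80%. The unpooled formula cannot reach 80% at any control size: its limit is Φ(0.08/√(0.09/97) − 1.96) = 74.7%.

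**Step 5: detectable difference.** Holding control at 2% and solving for 80% power with 97 vs 133 gives 9.0 points (pooled) or 9.8 points (unpooled), against the planned 8.

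**Step 6: audio versus control.** At 25% vs 2% with 97 and 133, pooled power is 99.9% per region, ignoring clustering.

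**Step 7: clustering, illustration only.** The document gives no intracluster correlation. Using a design effect of 1 + (m − 1) × ICC with m = 97 and 133, pooled-formula power is:

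| Assumed ICC | One region | Both regions |
|---|---|---|
| 0.005 | 55% | 83% |
| 0.01 | 43% | 71% |
| 0.02 | 30% | 52% |
| 0.05 | 17% | 29% |

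These figures still ignore the very few degrees of freedom left by one LGA per arm per region.

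**The case against.** The strongest reply is that the trial recruits in two regions. Combined, written versus control has 194 against 267 analysed and 93–95% power by the normal formulas. The primary objective is stated for Nigeria, and the document never expressly attaches the 80% to a region. A reader might infer from the mismatch that the whole trial falls below 80% before clustering. The arithmetic does not support that, and the point is confined to the region level. The per-region reading is itself an inference, though a natural one, because the full calculated sizes are applied within each state. The combined figure is limited reassurance, since it assumes independent individuals in a trial that randomises six LGAs.

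A reader might also extend the shortfall to every intervention-versus-control comparison. Audio versus control stays above 99% per region at the assumed proportions, so only written versus control is affected.

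A third tempting reading is that loss was handled wrongly, by multiplying by 1.15 instead of dividing by 0.85. The document gives no formula, and the unpooled route with division by 0.85 fits about as well as the pooled route with multiplication by 1.15. On the unpooled route the 97 retained in each intervention arm meets the 96.8 required. No loss error can be claimed.

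Two further objections stand in part. No single power value is correct: 68%, 74% and 78% depend on the method, and under the pooled formula the shortfall appears only after loss. But the plan states its 80% with the 15% loss included. Clustering is also the larger problem, since an assumed ICC of 0.01 costs far more than this mismatch. That limits how much the correction matters, but it does not make 114 against 157 consistent with the stated calculation.

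**Conclusion.** The point holds at the region level. The 10% versus 2% calculation requires 157 in both written and control, and the plan supplies 157 and 114. Two-sided per-region power after 15% loss is about 68% (unpooled), 74% (pooled) or 78% (exact), against a stated 80%. By the normal formulas the detectable difference is about 9 to 10 points, not 8. This rests on the plan's own proportions and loss rate, on two-sided testing, and on individuals being independent within LGAs. The last assumption favours the plan, so real power would be lower. The finding is a mis-stated power for one comparison. It does not show that the combined trial is below 80% under independence, that audio versus control is underpowered, or that loss was inflated wrongly.

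**What to change.** Revise the sample size paragraph as follows.

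1. State whether the 80% applies to each region or to the whole trial.
2. Restate per-region written-versus-control power as about 68–78% under the planned sizes, name the formula and sidedness, and replace the planned sizes with the actual per-arm baseline counts from the 811 enrolled. The article does not report those counts by arm.
3. Label the figure as before any allowance for clustering, and do the same for any combined-region figure.
4. Do not present 157 as giving 80% power against a 114-person arm.

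The cost is one corrected paragraph and a short recalculation. Baseline data collection is complete, and no extra enrolment is needed.
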